## Abstract

**Background:**

In a working population, common mental complaints like depressed mood and chronic fatigue are highly prevalent and often result in further deterioration of mental health and consequently absence from work. In a large occupational health setting, we will evaluate the (cost-) effectiveness of a Minimal Psychological Intervention (MPI), in reducing symptoms of depression and chronic fatigue in a working population. The MPI is also evaluated regarding its appreciation by worker, nurse, and occupational health physician (process evaluation). The tailor-made intervention is administered by nurses, who are trained in the principles of cognitive behavioural therapy and self-management.

**Methods/design:**

The presented WoPaCoM study (Work Participation of Workers with Common Mental complaints) is a two-armed randomized controlled trial, comparing MPI with usual care. A total number of 124 workers suffering from (chronic) mental fatigue or mild to moderate depression will be included. A stratified and block randomization will be applied, stratifying by customer organisation, income, and gender, using a block size of four. It will include a baseline measurement and subsequently follow up measurements after 4, 6 and 12 months. The primary outcome measures are symptoms of either fatigue (using the Checklist Individual Strength) and/or depression (using the Beck Depression Inventory) and secondary outcome measures include sickness absence, self efficacy, costs and quality of life. Analysis will include both univariate and multivariate techniques and data will be analysed according to the intention to treat principle.

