### Analysis

Data will be analysed according to the intention to treat principle. Despite participants dropping out of the intervention or not returning follow-up questionnaires, each individual is analysed as randomized (either control or intervention). We tried to encourage (potential) drop-outs to return their questionnaires in order to have complete data as much as possible. But if this was not possible, available (but not complete) data will still be included in the multilevel repeated measures analysis; this type of analysis better allows incomplete data. Finally, in the forthcoming articles, we will give full insight into the response rates at all phases of the study and consideration of the extent to which this might have caused specific biases.

Changes in primary and secondary outcome measures between the intervention and the control group will be analysed using both univariate and multivariate techniques. Models will be adjusted for baseline differences, age, gender, and socioeconomic status. Potential additional confounding factors and effect modifiers (covariates) will be checked separately and when necessary included in the model. If numbers permit, subgroup analyses will study the robustness of the findings across organizations and workers with a low and high income.

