### Power calculation

Using an individual randomization scheme, assuming an α of 0.05, a 1 – β of 0.90, and a decrease in symptoms of depression and/or fatigue of 25 percent in the intervention group versus a 5 percent decrease in the control group, 62 persons per arm were needed. As we expected that 25% percent would stop participating after baseline (attrition), 83 persons per arm had to be initially recruited [50,51].

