### Future implementation

If this intervention proves to be effective in reducing depression and fatigue and in improving quality of life, implementation of the intervention in the occupational health care system is considered and anticipated. An implementation and dissemination plan will be developed that might be of use for dissemination beyond the study plant. Additional arguments for such dissemination and implementation could be derived from positive changes in sick leave data and productivity figures.

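### Two primary outcomes are joined by *and/or* under one undivided α of 0.05 and one power of 0.90, without fixing whether one scale or both must succeed

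*Protocol article*

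**What the plan says.** Three places in the protocol article bear on what counts as a primary result.

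- Abstract, Methods/design: "The primary outcome measures are symptoms of either fatigue (using the Checklist Individual Strength) and/or depression (using the Beck Depression Inventory".
- Power calculation: "assuming an α of 0.05", "a 1 – β of 0.90", and one assumed effect, "a decrease in symptoms of depression and/or fatigue of 25 percent in the intervention group versus a 5 percent decrease in the control group". From these, "62 persons per arm were needed".
- Effect evaluation (main text): CIS-20 fatigue and BDI depression are both listed as primary, joined by a plain *and*.

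The Analysis section says that changes in outcomes "will be analysed using both univariate and multivariate techniques" and refers to a multilevel repeated measures analysis that uses incomplete data. It does not say how the two primary scales combine into a conclusion. α appears only in the power calculation and is not divided between the scales.

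**The concern.** With two primary scales, a single α and a single power describe the trial only once the rule for combining the scales is known. *And/or* leaves that rule open, and the main text reads differently from the abstract and the power calculation.

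The same data can therefore be positive under one reading and negative under the other, for instance if fatigue improves and depression does not. Under the either-scale reading the error rate exceeds the 5% used for planning. Under the both-scales reading the 90% power need not apply to the claim. The article links a positive result to possible use in occupational health care, so readers need to know beforehand what positive means.

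**Working it through.** **Inputs from the Power calculation:** α = 0.05, power = 0.90, 25% versus 5%, 62 per arm, 25% attrition, 83 per arm to recruit. Equal allocation is from Randomisation.

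**Assumptions:** tests are two-sided (the article does not say; two-sided reproduces 62). The correlation between the two test statistics is not given, so a range is shown.

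**1. The plan's own figure.** Treating 25% and 5% as proportions, with unpooled variance and no continuity correction:

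n = (z₀.₉₇₅ + z₀.₉₀)² × [p₁(1−p₁) + p₂(1−p₂)] / (p₁−p₂)²
= (1.960 + 1.282)² × (0.25×0.75 + 0.05×0.95) / 0.20²
= 10.507 × 0.235 / 0.04 = 61.7, so 62 per arm.

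With attrition: 62 / 0.75 = 82.7, so 83. Both stated figures are reproduced. They correspond to one comparison at an undivided 0.05.

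**2. Either scale suffices, each tested at 0.05.** Independent tests: 1 − 0.95² = 0.0975. For correlated tests, the probability that at least one of two bivariate normal statistics exceeds 1.960 in absolute value is:

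| Assumed correlation | False-positive rate |
|---|---|
| 0 | 9.75% |
| 0.3 | 9.5% |
| 0.5 | 9.1% |
| 0.7 | 8.3% |
| 0.9 | 7.0% |

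**3. Both scales required, each tested at 0.05.** The false-positive rate is at most 5%. If each scale has 90% power, joint power is 0.90² = 81% for independent tests, about 83% at correlation 0.5, about 85% at 0.7, and 90% only at perfect correlation.

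**4. Power at the strictest Holm step, 0.025.** With the formula that gives 62:

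SE = √(0.235/62) = 0.0616; 0.20/0.0616 = 3.249.
At 0.05: Φ(3.249 − 1.960) = 90.1%.
At 0.025: Φ(3.249 − 2.241) = 84.3%.

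Keeping 90% at 0.025 would need (2.241 + 1.282)² × 0.235/0.04 = 72.9, so 73 per arm, or 73/0.75 = 97.3, so 98 per arm before attrition.

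**The case against.** The strongest reply is that this is a condensed article, that an analysis plan may exist, and that multiplicity rules commonly sit there. That would settle the matter if the article were silent. It is not: it words the primary endpoint in two ways and sizes the trial on the looser one. A plan that splits α would not match the stated power. A plan that requires both scales would match it only if the tests were perfectly correlated or each scale had more than 90% power. The wording needs reconciling either way.

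A second reply is that *and/or* merely echoes the eligibility criteria, since workers could enter with either complaint. That is possible. It is also possible that 62 was meant for one combined responder comparison, for which the error rate would be 5%; the formula that reproduces 62 fits that. But no responder definition is given, and the primary outcomes are named as two scale scores, so neither reading is established. This limits the point to a conditional one.

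A reader might go further and infer six tests, two scales at three follow-ups, with an error rate of about 15% to 26.5%. The document does not support this. No section says that each follow-up is tested separately at 0.05, and the multilevel repeated measures analysis can yield one test per scale. Likewise, univariate and multivariate techniques may simply mean unadjusted and adjusted analyses; nothing says that either may decide success. Finally, the Future implementation sentence, "If this intervention proves to be effective in reducing depression and fatigue and in improving quality of life", might be read as a competing success rule that adds quality of life. It is discussion prose about possible roll-out and should not be treated as a decision rule.

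**Conclusion.** The point holds in conditional form. The article does not fix whether one primary scale or both must succeed, and it pairs that open wording with one α of 0.05 and one power of 0.90.

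- Either scale suffices, each tested at 0.05: false-positive rate of about 7.0% to 9.75%, not 5%.
- Both required: error at most 5%, joint power of about 81% to 90%.

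The ranges rest on assumed correlations from 0.9 down to independence for the first, and from independence to perfect correlation for the second. They also assume two-sided tests, one test per scale, and, for joint power, 90% power on each scale, which the article does not state separately. It cannot be said outright that the 5% level is breached, because that depends on a rule the document leaves open.

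**What to change.** State the success rule. The recommended form:

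1. Name one between-arm contrast per scale from the multilevel repeated measures model already planned.
2. Test CIS-20 and BDI with Holm's procedure at overall two-sided 0.05: the smaller p-value against 0.025 and, if that passes, the other against 0.05.
3. Claim an effect only on the scale or scales that pass.
4. Align the abstract, Effect evaluation and Power calculation with this rule, and restate the power.

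If the sponsor intends that both scales must succeed, each can stay at 0.05 without adjustment, but the article should say so and give the joint power.

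The change takes a few sentences and no new data. Its cost is power: at the strictest Holm step, 62 per arm gives about 84% (84.3%) instead of 90%. Restoring 90% would take 73 per arm, but the article reports that inclusion and data collection are closed, so the realistic course is to report the lower power. The rule should be fixed before outcomes are compared by arm.

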**Discussion:**

Patient recruitment in an occupational setting proves to be complicated and time consuming. Shift work for instance proved to be an obstacle for making appointments for consultation with the nurse. Furthermore, economic developments might have created job insecurity which negatively influenced participation in the study, with workers being anxious to be detected as having psychological problems. Additionally, long-term follow-up in a working population is time-consuming and continuously engages occupational health staff and administrative personnel to control the process of data gathering. However, if the intervention proves to be effective, occupational medicine will have a manageable option for treatment of workers who are at risk of loss of productivity or sickness absence.

**Trial registration:**

Nederlands Trialregister NTR3162

## Background

Fatigue and psychological distress are fairly common symptoms in the working population [1-3]. Approximately 20% of the working population report symptoms that fit the concept of prolonged fatigue [4]. There is evidence that fatigue is correlated with lost productive work time and related costs [5,6]. Fatigue is a predictor of sickness absence [6], future disability pension [7], and even occupational accidents [8]. There is also evidence that workers visiting their GP with complaints of fatigue often have higher levels of depressive complaints [9-11]. Problematic is that such mental health complaints often go unrecognized in practice [4]. By ignoring these complaints, symptoms may increase and eventually result in sickness absence and work-related disability [12-14]. From a preventive point of view, it is essential not to wait until workers are reported ill. It is important to intervene at an early stage to obviate aggravation of complaints.

In cases of minor depression, drug-related therapy is not necessarily the first choice [15-17]. A number of evidence-based psychological interventions, such as cognitive behavioral therapy and self-management strategies, are preferable for such complaints. Based on these principles, we previously developed a Minimal Psychological Intervention, which – in order to decrease the physicians’ work pressure – can likely be carried out by specially-trained nurses [18-20]. In the DELTA Study (Depression in Elderly with Long-Term Afflictions), it was found that the MPI provided an additional professional tool for nurses who cared for the chronically ill elderly persons with mild to moderate depressive symptoms [21]. The MPI was found both acceptable and feasible. The intervention improved quality of life and reduced the depressive symptoms [22,23].

In the current study, we set out to examine whether the MPI – as delivered by occupational nurses – is equally effective in a working population aimed at workers’ complaints of both depressive symptoms and fatigue. In this WoPaCoM study (Work Participation of workers with Common Mental complaints) we had the following main research questions:

1. What is the effect of the occupational nurse-delivered MPI on the mental health status, quality of life, and labor participation of workers with (symptoms of) mental fatigue and/or mild to moderate depressive symptoms, in comparison with care as usual?

2. How do workers, occupational nurses, and occupational physicians appreciate the intervention? What possible barriers regarding implementation do they experience?

## Design and methods

### Design

WoPaCoM is a study conducted in an Occupational Health Service in the South of The Netherlands that started at the end of 2007. Data gathering was finished in 2012. The customers of this service have their activities in the chemical industry. The two main customer organizations consist of approximately 6,000 workers in several settings, jobs and positions, varying from white and blue collar workers to researchers and administrative personnel. The WoPaCoM study is a two-armed (stratified) randomised controlled trial (with a block size of 4), evaluating the effectiveness of the MPI, including a process evaluation, for decreasing symptoms of fatigue and depression. After the baseline measurement, follow-up measurements at 4, 6 and 12 months are carried out (Figure 1). A total number of 124 participants will be included. The effect of MPI will be compared with care as usual. The ethics committee of the Maastricht University Medical Center found that the study was not subject to the Dutch Medical Research Involving Human Subjects Act (WMO): subjects were not subjected to invasive treatments, the subjects’ privacy was sufficiently guaranteed, and the setting was one in which regular occupational care was evaluated.

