## Discussion

### Progress of the study

In 2007, based on the occupational health service’s experience, it was estimated that it would take approximately two years to recruit participants. However, both the participation rates to the medical check-ups and the return rates of the screening questionnaires were smaller than expected and decreased substantially, particularly during the first phase of the economic crisis in Europe (2009). Increased perceptions of job insecurity might underlie these trends. Increasing efforts were needed to keep participants involved in the intervention itself, but also during the one-year follow-up. We ended inclusion in the study in April 2011 and the intervention has been administered to all participants in the intervention arm. Data collection was completed in June 2012. 127 Participants have completed their follow-up questionnaires. Of all participants initially included in the study 93% were male and 7% female (which was expected given the gender distribution in the plants). As per the stratified and blocked design, there is an equal number of intervention and control participants in the different strata.

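### The abstract and Design section give 124 as the number to be included, but the Power calculation needs 166 recruited to leave 124 after attrition

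*Protocol article*

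**What the plan says.** The protocol article gives the planned size in three places.

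- Abstract, Methods/design: "A total number of 124 workers suffering from (chronic) mental fatigue or mild to moderate depression will be included".
- Design section: "A total number of 124 participants will be included".
- Power calculation: "assuming an α of 0.05, a 1 – β of 0.90", with an effect of "a decrease in symptoms of depression and/or fatigue of 25 percent in the intervention group versus a 5 percent decrease in the control group", leads to "62 persons per arm were needed". Because 25% are expected to stop after baseline, the section then requires that "83 persons per arm had to be initially recruited".

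On what happened, the Progress of the study section reports "127 Participants have completed their follow-up questionnaires". It does not say how many were randomised.

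**The concern.** The Power calculation separates two quantities: the number that must remain (62 per arm, 124 in total) and the number that must enter so that enough remain (83 per arm, 166 in total). The abstract and Design section take the first and describe it as the second.

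The wording cannot easily be read another way. The Progress section uses *inclusion* and *included* for entry to the trial: it dates the end of inclusion and describes the sex split of those initially included. Nor can *recruited* in the Power calculation mean merely screened. The attrition it allows for is counted after baseline, and the Randomisation section places allocation after the baseline questionnaire. Both labels therefore describe the same stage, with different numbers.

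At stake is a core design figure. A reader who takes 124 from the abstract as the randomisation target and 90% from the Power calculation as its power holds two statements that cannot both be true under the article's own attrition assumption.

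**Working it through.** **Inputs from the Power calculation.** Alpha 0.05; power 0.90; 25% versus 5%; 62 per arm needed; 25% attrition after baseline; 83 per arm to recruit. Allocation is 1:1 (Randomisation section). The number to be included, 124, comes from the abstract and Design section.

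**Assumptions.** The article names no test, no sidedness and no standard deviation. I read 25% and 5% as proportions compared two-sided, because that reading reproduces the stated 62.

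**Step 1: reproduce 62 per arm.** Unpooled two-proportion formula:

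n = (p1q1 + p2q2)(z₀.₉₇₅ + z₀.₉₀)² / (p1 − p2)²

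= (0.25×0.75 + 0.05×0.95) × (1.960 + 1.282)² / 0.20²

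= 0.235 × 10.51 / 0.04 = 61.7, so 62 per arm. This matches exactly. Other two-sided versions come close but miss: 60 with the arcsine transformation, 65 with pooled variance under the null.

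**Step 2: reproduce 83 per arm.** 62 / (1 − 0.25) = 82.7, so 83 per arm and 166 in total. This also matches exactly. Check: 166 × 0.75 = 124.5, so 124 is what remains after attrition.

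**Step 3: the gap.** 166 − 124 = 42 participants between the two planned sizes.

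**Step 4: the conditional case in which only 124 are randomised.** 124 × 0.75 = 93, or 46 to 47 per arm. If drop-outs contribute nothing, the unpooled power is Φ(0.20 / √(0.235/n) − 1.960):

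- n = 46: Φ(2.798 − 1.960) = 0.799
- n = 47: Φ(2.828 − 1.960) = 0.807

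| Two-sided method | Power at 46 to 47 per arm |
|---|---|
| Unpooled (reproduces 62) | 79.9% to 80.7% |
| Pooled | 77.5% to 78.4% |
| Arcsine | 81.6% to 82.4% |
| Standardised effect set to give 90% at 62 per arm | 79.7% to 80.6% |

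The last row does not need the proportions reading. A one-sided version of that calibration gives about 81%. So about 80% depends little on the inferred formula.

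**Step 5: what the reported progress shows.** With 127 participants having completed follow-up, at least 127 entered, which already exceeds 124. If attrition had been exactly the planned 25%, 127 / 0.75 = 169 would have been randomised, close to 166. The observed attrition is not given, however, and 127 completers fit any enrolment of 127 or more.

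**The case against.** The strongest reply is that nothing went wrong in the design. The Power calculation is the only derivation of the sample size, it handles attrition correctly, and its 90% is properly supported there. Recruitment is over and the completers exceed the 124 needed. On that view this is one label in two places. Most of this stands, and it limits the point to a contradiction between stated sizes. It does not remove the contradiction, because the sample size is a figure on which readers of the trial rely.

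Three stronger readings are tempting but not supported.

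- *The trial is underpowered, at 80%.* That holds only if 124 were randomised and a quarter gave no data. The 127 completers rule out an enrolment of 124. The Analysis section also keeps available incomplete data in the multilevel repeated measures model, so even in the hypothetical case the loss may be smaller than a completers-only calculation gives.
- *The intention-to-treat population is misstated by 42, or the final report will use the wrong denominator.* The article states no intention-to-treat size. The Analysis section analyses each person as randomised, and nothing ties a denominator to 124. The 42 separates two planning targets.
- *Omitting the number randomised is itself a fault.* The Analysis section defers response rates at all phases to later articles, and the content of the flow chart (Figure 1) is not visible here. That detail may properly be reported elsewhere.

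**Conclusion.** The point holds as an internal contradiction: the abstract and Design section plan for 124 to enter, while the Power calculation plans for 166 to enter and about 124 to remain. The difference is 42 participants. It rests only on the article's own figures, and 62 and 83 per arm both reproduce. The likelier explanation is a mislabelled target, and actual underpowering is not shown.

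The drop from 90% to about 80% power (78% to 82%) is conditional. It requires 124 to have been the true randomisation target, 25% to be lost with no information retained, and a two-sided comparison of 25% with 5% as proportions. That last reading is inferred from the match to 62 and is not stated in the article.

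**What to change.** In the abstract and the Design section, replace 124 to be included with 166 to be randomised (83 per arm), to leave about 124 with follow-up after 25% attrition.

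If 124 really was the randomisation target, leave those two statements and correct the Power calculation instead. Remove the 83 per arm as the recruitment target and restate the power as about 80% (78% to 82%), with the test, the sidedness and the treatment of drop-outs written out. Add that power would be somewhat higher if the multilevel model draws on partial data.

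The cost is a text correction. No added enrolment is needed and no planned analysis changes.
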